###### Paired-Pulse TMS

A total of 2 TMS pulses, conditioning stimulus, and test stimulus, delivered at specific interstimulus intervals result in either facilitation or inhibition. In short-interval intracortical inhibition, MEP elicited by test stimulus is inhibited when preceded by a conditioning stimulus at ~1- to 5-millisecond intervals. In long-interval intracortical inhibition, the interstimulus interval is kept between 50 and 200 milliseconds, whereas in intracortical facilitation, the interval is ~10-30 milliseconds [15].

##### Psychosocial Parameter Outcomes

Visual Analog Scale (VAS) measures the perceived intensity of pain on a self-explanatory scale of 0 to 10, where 0 (no pain) to 10 (severe pain) [16].

The Beck Depression Inventory-II (BDI-II) is a 21-question multiple-choice self-report inventory to measure the presence and severity of depression. The cut-off scores with 0-9 indicating normal, 10-19 indicating mild depression, 20-30 indicating moderate depression, and 31-63 indicating severe depression [17].

The State-Trait Anxiety Inventory (STAI) is a 40-item self-report scale, commonly used to measure anxiety [18].

The World Health Organization Quality of Life-BREF (WHOQOL-BREF) Scale was developed in the context of the 4 domains defining the QOL: physical, psychological, social, and environmental. The higher the QOL score, the higher the life satisfaction [19].

##### Biochemical Quantification

The disruption of the blood-spinal cord barrier and secondary damage following the injury releases several chemokines, growth factors, and neurotransmitters in cerebrospinal fluid and systemic circulation, which could help predict the severity of the injury. The released components, such as myelin basic protein (MBP), interleukins, phosphorylated neurofilaments, brain-derived neurotrophic factor, Fas-ligand, gamma-aminobutyric acid, and glutamate, may serve as potential biomarkers for remyelination, inflammation, neuronal survival, and excitatory or inhibitory neurotransmitters after SCI [20-23]. Liquid chromatography and tandem mass spectrometry and enzyme-linked immunosorbent assays will be performed to quantify these biomarkers in plasma and serum samples.

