**Methods:**

A total of 40 patients with cSCI with American Spinal Injury Association (ASIA) grade A, aged 18-60 years, were randomly assigned to 5 groups. To evaluate the efficacy of iTBS versus traditional repetitive transcranial magnetic stimulation, patients were categorized into placebo, repetitive transcranial magnetic stimulation, and iTBS. In addition, to determine the optimal site for stimulation, groups were further subdivided into motor cortex, spinal cord, and combined. Each patient underwent 10 iTBS sessions twice daily for 5 consecutive days. Neurological outcomes and functional outcome parameters will be assessed. Electrophysiological evaluations included transcranial magnetic stimulation single-pulse and paired-pulse parameters. The effect of iTBS intervention on biomarkers will be quantified using the enzyme-linked immunosorbent assay, while neurotransmitters will be quantified by liquid chromatography and tandem mass spectrometry. Measurements will be done before and after the intervention, with follow-ups at 1, 2, and 3 months.

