## Methods

### Study Design

A double-blinded, prospective, randomized, placebo-controlled study will be conducted. The computer-generated sequence will be sealed in sequentially numbered envelopes, which will be opened after the patient is enrolled in the study. Both the patient and investigator will be blinded to the intervention. An experienced therapist will perform the intervention protocol. This protocol is based on the SPIRIT (Standard Protocol Items: Recommendations for Interventional Trials) guidelines (checklist provided in Multimedia Appendix 1).

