### Inclusion and Exclusion Criteria

Adults aged 18 to 60 years with a thoracolumbar (T1-L5) SCI and complete motor loss below the lesion level (American Spinal Injury Association [ASIA] score A) will be screened and recruited within 1 month of injury.

Exclusion criteria include patients with osteoporotic fractures, a history of neurological or orthopedic diseases affecting the SC, head injuries, ferromagnetic metallic implants near the target stimulation area, pacemakers, cognitive impairment, pregnancy, a history of seizures, or acute eczema or bedsores.

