### Patient Recruitment and Parameter Recording

Participants will be enrolled from the Jai Prakash Narayan Apex Trauma Centre at AIIMS (All India Institute Of Medical Sciences) Delhi. Following SCI surgery, a 15-day period will be designated for vertebral stabilization, after which sutures will be removed on the 15th day. Once the sutures are removed, baseline parameters will be measured. Patients will then be randomly assigned to one of the intervention groups. After completing the intervention, postintervention parameters will be recorded and follow-up assessments will be conducted at 1, 2, and 3 months (Figure 2). To ensure consistency during the intervention, all assessments will be recorded by the blinded primary investigator.

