#### Statistical Analysis

Data will be analyzed using STATA 14.0 software (StataCorp). Continuous variables will be presented as mean and SD, and categorical variables as frequencies and percentages. The primary analysis will be the intention-to-treat analysis, where baseline values will be carried forward for subjects with missing data. Unless stated otherwise, intention-to-treat data will be presented throughout the study. In addition, a per-protocol analysis will be conducted, including only participants who comply with the protocol.

Normality will be evaluated using the Shapiro-Wilk test for each outcome, homogeneity of variance will be checked using the Levene test, and the Mauchly test will be used for sphericity. Depending on the data distribution, parametric or nonparametric tests will be applied.

If the data are found to be uniformly distributed, we will use repeated measures ANOVA to assess changes over time within and between groups. Bonferroni or Tukey correction will be done for post hoc pairwise comparisons. Nonparametric tests like the Friedman test followed by appropriate post hoc tests will be used for skewed data. Corrections for multiple comparisons will be applied as specified to reduce the risk of type I errors. To analyze categorical variables, the chi-square or Fisher exact test will be used to assess associations between groups.

A *P* value less than .05 with a 95% CI will be considered statistically significant.

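### Biomarker baselines fall at different times after injury, so within-arm changes cannot show a stimulation effect; rest conclusions on the between-arm contrast, adjusted for days since injury

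*Protocol article*

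**What the plan says.** **Eligibility.** Under Inclusion and Exclusion Criteria, patients "will be screened and recruited within 1 month of injury".

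**Baseline.** Patient Recruitment and Parameter Recording states: "Following SCI surgery, a 15-day period will be designated for vertebral stabilization, after which sutures will be removed on the 15th day". It continues: "Once the sutures are removed, baseline parameters will be measured". Randomisation comes after that: "Patients will then be randomly assigned to one of the intervention groups". The interval from injury to surgery is not fixed.

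**Later measurements.** The Methods paragraph of the abstract ties them to the intervention: "Measurements will be done before and after the intervention, with follow-ups at 1, 2, and 3 months". I take this schedule to cover the blood draws, since the article gives no separate one.

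**Rationale for the markers.** Biochemical Quantification says: "The disruption of the blood-spinal cord barrier and secondary damage following the injury releases several chemokines, growth factors, and neurotransmitters". The listed markers are to be measured in plasma and serum. The section does not say whether they rise or fall after injury, or how fast.

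**Analysis.** In Statistical Analysis, for data that meet the distributional check, "we will use repeated measures ANOVA to assess changes over time within and between groups". For skewed data the only test named is the Friedman test. The section contains no term for time since injury.

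**Control.** Study Design provides a concurrent placebo arm: "A double-blinded, prospective, randomized, placebo-controlled study will be conducted".

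**The concern.** If an injury puts a marker into the blood, its level may depend on how long ago the injury happened. Two patients at the same study visit can be two to four weeks apart on that scale. A before-after change within an arm then contains whatever the marker would have done untreated, and the amount of natural change can differ from patient to patient.

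The analysis sentence gives within-group and between-group change equal standing. A fall in an inflammatory or neuronal-damage marker within an iTBS arm could be read as a benefit of stimulation when it is only the course of the injury. Between arms, unequal timing can arise by chance with 8 patients each, and the timing spread adds to the error variance.

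**Working it through.** **1. The plan's own figures.** The article gives no number for biomarkers or for time since injury. The input it does supply is 8 patients per arm, which comes from the motor evoked potential calculation. That reproduces: for a difference of 13.53 − 12.85 = 0.68 and SD 0.3, exact t-test power is 0.879 with 5 per group and 0.942 with 6. Then 6 / 0.8 = 7.5, rounded up to 8, and 8 × 5 = 40.

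**2. Range of the baseline day** (1 month taken as 30 days).
- Earliest: surgery on the day of injury, 0 + 15 = day 15.
- Latest, if recruitment means the baseline visit: day 30.
- Latest, if a patient is recruited at 1 month and only then has surgery: 30 + 15 = day 45.

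**3. Chance imbalance between two arms of 8** (assumption: baseline day uniform over the window). The SD of one patient's baseline day is width / √12. The SD of the difference in arm means is that value × √(2/8), that is, half of it.
- Day 15–30: 15 / √12 = 4.3 days; difference SD 2.2 days; 95% range ± 4.2 days; a difference above 5 days in 2% of trials.
- Day 15–45: 30 / √12 = 8.7 days; difference SD 4.3 days; 95% range ± 8.5 days; a difference above 5 days in 25% of trials.

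**4. Effect on inference when there is no treatment effect.** Simulation of 5 arms of 8, with 2,000 trials per scenario. All the following are assumptions, not taken from the article: log marker = log(0.2 + exp(−kt)), with t in days since injury and k = ln 2 / half-life; between-patient SD 0.4; residual SD 0.3; draws at 0, 5, 35, 65 and 95 days from baseline. The paired t, two-arm t and SD columns use the change from baseline to the last draw. The Friedman column uses all five draws in one arm. The adjusted SD adds days since injury at baseline as one covariate.

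| Window (days) | Half-life (days) | One arm, paired t: P<.05 | One arm, Friedman: P<.05 | iTBS v placebo, t test: P<.05 | SD of change, unadjusted → adjusted |
|---|---|---|---|---|---|
| 15–30 | 15 | 1.000 | 1.000 | 0.050 | 0.442 → 0.425 |
| 15–30 | 30 | 1.000 | 1.000 | 0.047 | 0.428 → 0.425 |
| 15–30 | 60 | 0.991 | 0.984 | 0.054 | 0.424 → 0.424 |
| 15–45 | 15 | 0.986 | 0.992 | 0.053 | 0.476 → 0.426 |
| 15–45 | 30 | 1.000 | 1.000 | 0.054 | 0.435 → 0.424 |
| 15–45 | 60 | 0.983 | 0.982 | 0.046 | 0.425 → 0.424 |

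The five-arm ANOVA of change rejected in 0.044 to 0.056 of trials. The mean iTBS-minus-placebo difference lay between −0.003 and 0.008 log units, so there was no bias.

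**5. Reading the table.** Under an assumed decline, a test within one arm is significant almost every time with no treatment effect. The between-arm test keeps its 5% level without any adjustment. Adjustment lowers the residual SD by (0.442 − 0.425) / 0.442 = 4% or (0.476 − 0.426) / 0.476 = 11% at a 15-day half-life. At 30 days the reduction is 1 to 3%, and at 60 days it is practically nil.

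**The case against.** The strongest reply is that randomisation already deals with this. Days since injury is settled before allocation, and a sham arm is followed on the same schedule, so natural course is shared across arms in expectation and chance imbalance is already reflected in the standard error. This stands. A reader might infer that every unadjusted biomarker comparison is confounded by time since injury; the design does not support that for comparisons between arms.

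Second, the article never says that the markers decline. It says that injury releases them, and it lists growth factors and neurotransmitters that need not follow one pattern. This also stands. Any half-life is an assumption, and the size of the effect will differ by marker. The day-45 limit is only one reading of the recruitment rule, and a uniform spread up to that day is a further assumption.

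Third, an article leaves covariate lists to a full protocol or analysis plan. That is fair, and the absence of a covariate is not the point on its own. The point is that the stated analysis puts within-group change alongside the randomised contrast for outcomes whose stated source is the injury itself.

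Fourth, within-arm change would be uninterpretable even if every patient had the same baseline day, and no passage says that conclusions will rest on it. Both are true. The covariate does not rescue a within-arm comparison, which is why the first part of the fix concerns which contrast is interpreted. The limits of a purely within-patient test such as Friedman's also reach beyond the biomarkers.

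**Conclusion.** The point holds in a limited form. The spread in baseline timing follows from the article: about day 15 to about day 30 after injury, or to about day 45 on the looser reading. If a marker changes over the weeks after injury, within-arm changes cannot be attributed to stimulation. In the assumed scenarios they were significant in 98 to 100% of trials with no treatment effect.

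Between-arm contrasts are valid as planned. What they lose is some precision, with exposure to a chance difference in mean baseline day (SD 2.2 to 4.3 days under uniform timing, 8 per arm). Adjustment recovers about 4 to 11% of the residual SD under a fast decline and almost nothing under a slow one. These are secondary outcomes, so this is an inexpensive improvement and not a threat to the trial's main conclusion.

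**What to change.** In Statistical Analysis, add a statement for the biochemical outcomes along these lines:

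- Conclusions rest on the between-arm contrast with placebo at the post-intervention visits. Within-arm changes are descriptive only.
- The model includes the baseline marker value and the days from injury to the baseline draw as covariates. Markers with skewed distributions are analysed on the log scale, which keeps a between-arm contrast available.
- Days since injury at baseline are reported by arm.

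An interaction of days since injury with visit is optional; with 8 per arm it need not be required.

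The cost is wording and one or two degrees of freedom: a single-visit comparison of 40 patients in 5 arms has 40 − 5 = 35 residual degrees of freedom, or 33 with both covariates. The date of injury is already needed to apply the 1-month rule, so no new data are collected.

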##### Physiotherapy

A trained physiotherapist will be assigned to provide individualized rehabilitation training for 5 days. After this period, patients will be instructed to perform the exercises independently at home, maintaining a logbook and submitting weekly videos of their performance for evaluation by the physiotherapist till the time of last follow-up (Figure 3).

**Figure 3 figure3:**
[figure not shown]
Outline of physical rehabilitation regime for patients with spinal cord injury. Exercise prescription and progression will be based on the individual’s performance and tolerance to baseline exercises. AROM: active range of motion; PROM: passive range of motion; RM: repetition maximum; SCI: spinal cord injury.

#### Statistical Analysis

Data will be analyzed using STATA 14.0 software (StataCorp). Continuous variables will be presented as mean and SD, and categorical variables as frequencies and percentages. The primary analysis will be the intention-to-treat analysis, where baseline values will be carried forward for subjects with missing data. Unless stated otherwise, intention-to-treat data will be presented throughout the study. In addition, a per-protocol analysis will be conducted, including only participants who comply with the protocol.

Normality will be evaluated using the Shapiro-Wilk test for each outcome, homogeneity of variance will be checked using the Levene test, and the Mauchly test will be used for sphericity. Depending on the data distribution, parametric or nonparametric tests will be applied.

If the data are found to be uniformly distributed, we will use repeated measures ANOVA to assess changes over time within and between groups. Bonferroni or Tukey correction will be done for post hoc pairwise comparisons. Nonparametric tests like the Friedman test followed by appropriate post hoc tests will be used for skewed data. Corrections for multiple comparisons will be applied as specified to reduce the risk of type I errors. To analyze categorical variables, the chi-square or Fisher exact test will be used to assess associations between groups.

A *P* value less than .05 with a 95% CI will be considered statistically significant.

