### Sample Size

The sample size for this study is determined based on the methodology outlined by Roy et al [8], which assessed the reduction in motor evoked potential (MEP) amplitude following intervention. Using an α level of 0.05 and a power of 90%, these parameters are incorporated into the 2-tailed formula for sample size calculation.

For a 2-sample comparison of means, the null hypothesis (H0: m1=m2) will tested, where m1 and m2 represent the means of 2 distinct populations. The assumptions for the calculation are as follows:

α=.05 (2-sided), Power=0.90, m1=12.85, m2=13.53, SD1=0.3, SD2=0.3, n2/n1=1.00

Based on these assumptions, the estimated required sample size is calculated to be 6 subjects per group. To account for potential dropouts, a 20% adjustment is applied, resulting in a revised sample size of 8 participants per group. Consequently, the total minimum sample size required for the study is 40 participants.

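### Carrying the baseline value forward as the primary missing-data rule treats every gap as no change, which dilutes a true effect and can bias the comparison if dropout differs between arms

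*Protocol article*

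**What the plan says.** The Statistical Analysis section fixes both the primary analysis set and its missing-data rule: "The primary analysis will be the intention-to-treat analysis, where baseline values will be carried forward for subjects with missing data". The rule reaches beyond the primary outcome: "Unless stated otherwise, intention-to-treat data will be presented throughout the study". The only other analysis named is a per-protocol one: "In addition, a per-protocol analysis will be conducted, including only participants who comply with the protocol".

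The Sample Size section starts from "α=.05 (2-sided), Power=0.90, m1=12.85, m2=13.53, SD1=0.3, SD2=0.3, n2/n1=1.00" and finds that "the estimated required sample size is calculated to be 6 subjects per group". It continues: "To account for potential dropouts, a 20% adjustment is applied, resulting in a revised sample size of 8 participants per group", and with five groups "the total minimum sample size required for the study is 40 participants".

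Three other sections bear on whether no change is a reasonable value to fill in:

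- Under Inclusion and Exclusion Criteria, patients with complete injuries "will be screened and recruited within 1 month of injury".
- Postintervention Care and Physiotherapy give rehabilitation to the placebo group too, with home exercises until the last follow-up.
- Patient Recruitment and Parameter Recording sets assessments after the intervention and at 1, 2 and 3 months.

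**The concern.** The rule assigns zero change to every gap and then analyses that value as if it had been measured. A patient seen at 1 and 2 months but not at 3 has the 3-month value filled from baseline, although two more recent measurements exist.

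The trial looks for recovery over the first months after injury, and all arms receive active rehabilitation. Some change from baseline is plausible in every arm, and the article offers no argument that patients who miss visits stay where they began.

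Three things are at stake:

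- A real effect is diluted.
- If arms lose patients at different rates and patients change over time, part of the estimated difference reflects dropout and not treatment.
- The dropout allowance is sized so that about 6 observed patients per arm carry the full difference. The primary analysis instead keeps 8 per arm, some of them entered as zeros.

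With 8 per arm, one or two missing patients are 12.5% or 25% of an arm. The per-protocol analysis is no safeguard: it selects on compliance after randomisation and does not address missing data.

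**Working it through.** **1. The plan's own figure.** Inputs from the Sample Size section: difference 13.53 − 12.85 = 0.68, SD 0.3, two-sided alpha 0.05, power 0.90, equal allocation. The standardised difference is 0.68/0.3 = 2.27.

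- Normal approximation: n = 2(1.96 + 1.2816)²/2.27² = 4.09, rounded up to 5.
- Exact t-test power: 87.9% at 5 per arm and 94.2% at 6 per arm, so 6 is right.
- Dropout: 6/(1 − 0.20) = 7.5, rounded up to 8; 5 × 8 = 40.

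The stated sample size reproduces.

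**2. What the rule does to the estimate.** Let *m*T and *m*C be the true mean changes, *p*T and *p*C the dropout probabilities, and let dropout be unrelated to outcome. With baseline carried forward:

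- Expected difference = (1 − *p*T)*m*T − (1 − *p*C)*m*C.
- Equal dropout *p*: (1 − *p*)(*m*T − *m*C). At *p* = 0.20 this is 0.8 × 0.68 = 0.544, or 0.8 × 2.27 = 1.81 SD.
- No true effect (*m*T = *m*C = *m*): (*p*C − *p*T)*m*. This is zero if dropout is equal or if nobody changes.
- Variance of one patient's analysed change, in SD units: (1 − *p*) + *p*(1 − *p*)*m*². At *p* = 0.20 this is 0.80 + 0.16*m*².

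The last line explains why power depends on recovery although the expected difference does not. With a control-arm change of 0, 1 or 2 SD, the control variance is 0.80, 0.96 or 1.44 and the treated variance 1.62, 2.51 or 3.71.

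**3. Power with 8 per arm and 20% random dropout in both arms.** Simulated two-sample t-test on change, with 0.3 taken as the SD of change. The control-arm change is an assumed range, because the article gives no figure.

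| Assumed control-arm change | Expected difference | Power, baseline carried forward | Power, observed data only |
|---|---|---|---|
| 0 SD | 1.81 SD | about 87% | about 94% |
| 1 SD | 1.81 SD | about 70% | about 94% |
| 2 SD | 1.81 SD | about 54% | about 94% |

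The observed-data analysis keeps the expected difference at 2.27 SD. With no dropout, power at 8 per arm is 98.8%. To regain 90% under baseline carried forward would take about 9 per arm with no control-arm change, and about 21 if the control arm changes by 0.68 (2.27 SD).

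**4. No true effect, 8 per arm.**

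| Assumed change in both arms | Bias, 10% v 30% dropout | Type I error, 10% v 30% | Type I error, 20% v 20% |
|---|---|---|---|
| 0 SD | 0 | about 5% | about 5% |
| 1 SD | 0.20 SD | about 7% | about 5% |
| 2 SD | 0.40 SD | about 10% | about 5% |

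The bias follows from (0.30 − 0.10) × *m* and favours the arm that loses fewer patients when change is improvement.

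**The case against.** **The recovery is assumed.** The article gives no recovery rate. It enrols only complete injuries, and its Background says that restoring function after such an injury is challenging. A reader might infer that the filled-in value is known to be wrong; the documents do not establish that. They also do not establish that it is right, which a primary rule needs. With no change in either arm there is no bias under the null, and even at 0.5 SD of change the 10% v 30% split gives a type I error of only about 6%. That split is itself an assumption.

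**The numbers are not for the primary outcome.** They use motor evoked potential inputs, treat 0.3 as the SD of change, and test two arms at one time point. The plan has an ASIA primary outcome, five groups and repeated-measures ANOVA. This stands: the figures are illustrative. The formulas in step 2 do not depend on the scale.

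**The rule is cautious.** Under equal dropout it shrinks the effect and leaves the type I error at about 5%, so a reader who infers that false positives or understated uncertainty follow in general would be going too far. The protection is lost once dropout differs between arms and patients change.

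**Two further readings go beyond the text.** One is that observed 1- and 2-month values are thrown away. The article does not say so; the natural reading keeps them and merely ignores them when filling a later gap. The other is that the Sample Size and Statistical Analysis sections contradict each other. Inflating for dropout and analysing by intention to treat is ordinary practice. What is true is narrower: the inflation does not compensate for dilution. With 10% dropout and no control-arm change, power is still about 94%.

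**A separate analysis plan may add sensitivity analyses.** It may, but the primary rule is chosen here.

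**Conclusion.** The point holds as a poorly justified primary rule, not as an error that certainly invalidates the result. Dilution by the dropout fraction is arithmetic whenever dropout is equal and unrelated to outcome, and needs no assumption about spontaneous recovery. Bias in either direction needs both change over time and unequal dropout; the article excludes neither, and arms of 8 make imbalance easy.

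At the allowed 20% dropout, illustrative power is below the planned 90% at every recovery level examined. The shortfall is small with no control-arm change (about 87%) and large at 2 SD (about 54%). How far this carries over to the ASIA scores cannot be computed, because the article gives no mean or SD for them.

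**What to change.** By a dated, justified amendment before unblinding:

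- Make the primary analysis of the ASIA motor and sensory scores a likelihood-based mixed model for repeated measures, using every observed visit of all randomised patients.
- Handle baseline so that a patient with no post-baseline value is not excluded by rule, for example by modelling baseline as part of the response with a mean common to all arms.
- Use a simple structured covariance with a small-sample degrees-of-freedom correction; an unstructured matrix asks much of 40 patients in five arms.
- Analyse the ASIA impairment grade (A to E) by a method suited to an ordinal outcome.
- Keep baseline carried forward as a sensitivity analysis.

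The cost is the amendment and the programming. No extra patients, visits or measurements are needed, and the named software fits such models. Because the Results section places analysis in January to July 2025, the timing relative to unblinding must be documented. The downside is reliance on data being missing at random, which the retained sensitivity analysis probes.

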### Experimental Groups

A total of 40 patients will be randomized into 5 groups using computer-generated random numbers. Patients will be categorized into placebo, rTMS, and iTBS to evaluate the efficacy of iTBS versus traditional rTMS on the primary motor cortex (MC). To determine the optimal site for iTBS application, stimulation was given at either MC or SC or combined MC+SC.

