### Limitations

While this study offers valuable insights, several limitations must be acknowledged that may affect the interpretation and broader application of the findings. First, the sample size is relatively small, which could reduce the statistical power and may not fully represent the broader population of individuals with SCIs. Second, variability in the severity of SC injuries among participants may influence the outcomes, as responses to treatment could differ based on the level and completeness of the injury. Finally, the short duration of the follow-up period may not adequately capture the long-term effects of the interventions, suggesting the need for longer-term studies to assess the sustainability of the benefits observed.

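### Repeated measures ANOVA without baseline adjustment, with Friedman as fallback, is a weak way to compare arms; a baseline-adjusted between-group model uses data already collected

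*Protocol article*

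**What the plan says.** The Statistical Analysis section of the Protocol article says that, when distributional checks allow, "we will use repeated measures ANOVA to assess changes over time within and between groups". Post hoc pairwise comparisons are to be corrected by Bonferroni or Tukey. For skewed data it names the Friedman test with post hoc tests. It names no covariate, and it does not say which term or contrast answers the efficacy question.

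Three other places bear on this:

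- **Visits.** The Abstract (Methods) lists five: before the intervention, after it, and at 1, 2 and 3 months.
- **Timing of baseline.** Patient Recruitment and Parameter Recording says "Once the sutures are removed, baseline parameters will be measured", and randomisation follows. Baseline is therefore a true pre-randomisation value.
- **Injury level.** Entry covers T1 to L5, all ASIA A. The Limitations section allows that "responses to treatment could differ based on the level and completeness of the injury".

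**The concern.** No treatment effect is possible at a visit held before randomisation. If that visit is one of the repeated outcomes, the group main effect averages in a zero. The effect then moves into the group-by-time interaction, a diffuse test over all arms and visits. Neither term uses baseline in the most efficient way, which is as a covariate.

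The Friedman test is a within-subject test with no group term. Bounded ASIA scores could well fail a normality check, in which case the fallback would apply to the primary outcome and would yield only within-arm results. Every arm also receives rehabilitation, placebo included (Postintervention Care; Physiotherapy), so change within an arm cannot be credited to stimulation.

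With 8 patients per arm, the trial can ill afford to lose precision on the comparison it was randomised to make.

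**Working it through.** **The plan's own figure.** The Sample Size section uses "α=.05 (2-sided), Power=0.90, m1=12.85, m2=13.53, SD1=0.3, SD2=0.3, n2/n1=1.00" and reports that "the estimated required sample size is calculated to be 6 subjects per group".

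- The standardised difference is 0.68/0.3 = 2.27.
- The normal approximation gives 2(1.960 + 1.282)² × 0.3²/0.68² = 4.09, rounded up to 5 per group.
- The noncentral t gives power 0.879 at n = 5 and 0.942 at n = 6, so 6 is reproduced.
- For dropout, 6/0.8 = 7.5 is rounded up to 8, and 5 × 8 = 40.

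This is an unadjusted two-group comparison of MEP amplitude. It contains no correlation or baseline term, and its effect size cannot be carried over to the ASIA outcome.

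**Inputs for the check.** From the documents: 5 arms of 8, and 5 visits of which the first precedes randomisation. Assumed, because the documents do not give them: equal correlation ρ between all visits, from 0.3 to 0.9, and a shift of 1 SD in one arm at every post-baseline visit.

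**Dilution and degrees of freedom.** The group main effect averages (0 + 1 + 1 + 1 + 1)/5 = 4/5 of the effect. Group-by-time has (5 − 1)(5 − 1) = 16 df.

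**Noncentrality.** With one arm of five shifted by 1 SD, the between-arm sum of squares is (0.8)² + 4(0.2)² = 0.8.

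- Group main effect (4, 35 df): λ = 8 × 0.8 × 0.8² / [(1 + 4ρ)/5]. At ρ = 0.5 this is 4.096/0.6 = 6.83.
- Group-by-time (16, 140 df): λ = 8 × 0.8 × 0.8 / (1 − ρ). At ρ = 0.5 this is 5.12/0.5 = 10.24.
- Baseline-adjusted omnibus test on the mean of the four post-baseline visits (4, 34 df): λ = 8 × 0.8 / [(1 + 3ρ)/4 − ρ²]. At ρ = 0.5 this is 6.4/0.375 = 17.07.
- One pairwise contrast at month 3: the variance factor is 1 − ρ² if adjusted (34 df) and 2(1 − ρ) for change from baseline (35 df). At ρ = 0.5 the noncentralities are 1/√(2 × 0.75/8) = 2.31 and 1/√(2 × 1/8) = 2.00.

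**Power at two-sided 0.05**

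| Test | ρ 0.3 | ρ 0.5 | ρ 0.7 | ρ 0.9 |
|---|---|---|---|---|
| Group main effect, baseline among visits | 0.61 | 0.47 | 0.38 | 0.31 |
| Group-by-time, 16 df | 0.29 | 0.42 | 0.68 | about 1.0 |
| Adjusted omnibus, post-baseline mean | 0.88 | 0.89 | 0.96 | about 1.0 |
| Adjusted single contrast, month 3, uncorrected | 0.53 | 0.61 | 0.78 | 0.99 |
| Change-from-baseline contrast, month 3, uncorrected | 0.38 | 0.49 | 0.71 | 0.99 |

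The first three rows are all omnibus tests and compare like with like. The last two are single contrasts and should be compared with each other. Charging for estimation of the baseline slope lowers the third row by about 0.01 at ρ 0.3 to 0.7.

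**Friedman within one arm.** This was simulated with 8 patients, no treatment effect, and a recovery common to all arms rising evenly to an assumed 1 SD at month 3. It rejects in 51%, 75% and 99.8% of runs at ρ 0.5, 0.7 and 0.9. With an assumed 0.5 SD recovery the figures are 16%, 22% and 61%.

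**Level as a covariate.** One binary term multiplies variance by about (1 − q)(1 + 1/32), where q is its partial R² after baseline. That is 1.03 at q = 0, 0.93 at q = 0.10 and 0.83 at q = 0.20. Entered as 17 separate levels (16 df), it multiplies variance by 1.94 at q = 0 and 1.36 at q = 0.30, a loss in both cases.

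**The case against.** Several points on the other side stand.

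- **Baseline as a visit is inferred.** The article never says it. The inference is reasonable given the visit list and the wording on change over time, but it remains an inference.
- **Between-group assessment is in the plan, with multiplicity correction.** A reader might infer that efficacy will be judged on within-group P values. The article does not say so. Nor does it say that spontaneous recovery is expected, so the recovery in the Friedman simulation is an assumption.
- **The gain depends on the comparison.** It is tempting to set 0.38 against 0.96 at ρ 0.7 as the benefit. The 0.96 belongs to the post-baseline mean. If month 3 is the primary time point, the figure is 0.78, against 0.71 for a plain change contrast that the repeated measures model can already supply. At ρ 0.3 with a constant effect, the single month-3 contrast (0.53) falls below the group main effect (0.61). Correction matters too: at ρ 0.7 the month-3 contrast drops from 0.78 to 0.57 with Bonferroni for 4 comparisons and to 0.43 for all 10 pairs.
- **Injury level.** A reader might call its absence from the model an error. A covariate list is something an article commonly leaves to the full protocol or SAP. The Limitations section says only that responses could differ, which suggests possible effect modification rather than a known prognostic effect. Chance-imbalance figures rest on an assumed case mix: the probability that some arm has no lumbar patient is about 36% if 10 of 40 are lumbar, but 85% for 6 and 7% for 15.

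None of this rescues Friedman as a comparison of arms, or shows that an unadjusted analysis with baseline among the outcomes is the better choice.

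**Conclusion.** The concern holds in a limited form. The article fixes an analysis that, on its natural reading, dilutes or diffuses the between-group question, and a fallback that cannot answer it. A baseline-adjusted between-group model is a concrete improvement. Among the omnibus tests it has clearly higher power at ρ 0.3 to 0.7, and it is level with group-by-time at ρ 0.9.

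It would be too strong to call this a free gain. Its size depends on a correlation that the documents do not give, on an assumed 1 SD constant effect, and on the chosen time point. Baseline is also not discarded by the planned model, only used inefficiently. The gain may be small for the lower-limb motor score, where baseline is near zero in thoracic ASIA A patients. It is nil for the impairment grade, since everyone enters as A. Baseline sensory score should largely follow injury level, so gains from the two covariates should not be added together.

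The sample size of 40 is unaffected. This is a change that should be made, not a flaw that invalidates the trial.

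**What to change.** 1. Make the primary analysis a between-group comparison of post-baseline ASIA score. Fixed effects: group, visit, group-by-visit and the baseline value. Random effect: patient.
2. Name one time point in advance, either month 3 or the mean of the post-baseline visits, and report the between-group difference there with its 95% CI. The post-baseline mean has more power if the effect is constant.
3. Keep the Bonferroni or Tukey correction already named, and apply it across the arm comparisons.
4. Report within-group change descriptively, without using it as evidence of efficacy.
5. For skewed data, replace Friedman with a between-group method such as a rank-based ANCOVA.
6. Optionally, add one coarse level term (thoracic v lumbar). It costs about 3% in variance if level is not prognostic and helps only if level predicts outcome beyond baseline. Do not enter level segment by segment.

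The cost is some analysis wording and about one degree of freedom per covariate. No extra patients, visits or measurements are needed.
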